## Abstract

**Background:**

Approximal surfaces are a challenge to caries lesions control. Silver diamine fluoride (SDF) is a simple,low-cost and promisor intervention for arresting caries lesions, but it has never been tested on approximal surfaces. Our aim is to evaluate the efficacy and cost-efficacy of SDF in arresting initial lesions compared to resin infiltration and exclusively flossing (control group). Our second aim is to assess discomfort and satisfaction regarding interventions.

**Methods/design:**

This is a randomized clinical trial, double-blinded, placebo-controlled study. Children/adolescents presenting at least one approximal initial caries lesion in primary molars/permanent premolars and molars will be included. Surfaces with advanced dentine lesions identified by radiography and participants who refuse to participate or present negative behaviors will be excluded. A minimum sample size of 504 surfaces will be required for each subgroup. Individuals will be randomly allocated in three groups of interventions: SDF, resin infiltration, and control group. Depending on the allocation, the patients will receive the active treatment and respective placebo therapies. All patients will be oriented to daily flossing the included surfaces. Our primary outcome will be caries progression by clinical and radiographic examinations. Appointments will be timed and costs of materials will be considered to calculate cost-efficacy. Patient discomfort will be assessed after interventions. Parent and patient satisfaction with the treatment will be collected after treatment and in the last follow-up visit. Individuals will be assessed at 1 and 3 months after treatment to evaluate dental biofilm and at 6, 12, and 24 months to assess caries progression by visual examination and/or radiography. Multilevel analyses will be used to verify if the type of treatment influenced on the tested outcomes. Costs will be compared and analyses of cost-efficacy will be performed. Poisson analysis will test the association between intervention and reported discomfort and satisfaction.

**Discussion:**

Our hypothesis is that SDF is the most cost-efficacious option from all tested interventions. If our hypothesis is confirmed, the use of SDF in private and public contexts could represent an easier and effective option in the treatment of enamel approximal caries in children/adolescents.

**Trial registration:**

ClinicalTrials.gov (NCT01477385), Initial release: 11/16/2011: last update: 06/02/2014.

**Electronic supplementary material:**

The online version of this article (doi:10.1186/1745-6215-15-448) contains supplementary material, which is available to authorized users.

## Background

Approximal surfaces are a challenge regarding the control of caries lesions due to the area of contact between them and limited salivary access [1, 2]. In addition, poor compliance to flossing by children and adolescents [3] contributes to difficulty in arresting approximal caries lesions.

Despite flossing being the most suitable method for mechanical removal of biofilm from the interproximal area [4, 5], the controlling of approximal caries just by flossing has not been shown to be effective [6], probably because its use by children and adolescents is not constant and adequate [3]. Thus, early interventions to initial caries lesions become even more important to arrest these lesions and prevent cavitations or their progression into dentine.

Recently, the use of silver diamine fluoride (SDF), an effective cariostatic agent used in caries prevention since 1960 [7], has been proposed to arrest enamel caries lesions [8, 9]. A previous study of our group showed the SDF efficacy in arresting enamel caries lesions on occlusal surfaces of erupting permanent molars [8], which are areas of difficult mechanical control of biofilm, much like the approximal surfaces. However, this cariostatic agent has not been tested in the arrest of approximal caries lesions.

Other options, such as sealants and resin infiltration, have been pointed as promisor to controlling approximal caries lesions [10]. The resin infiltrant is a novel low-viscosity resin that promotes sealing into the lesion [11]. Previous studies have shown caries infiltration to be an efficacious treatment for permanent and primary teeth [12–15], superior to exclusively flossing [12, 13] and probably even approximal sealing [14].

Contrary to SDF, resin infiltration requires the use of a rubber dam and clamps. Thus, we hypothesized the resin infiltration would result in higher costs and reduce patient acceptance for arresting initial caries than the use of SDF. Therefore, not only the efficacy but also the cost-efficacy and patient discomfort/satisfaction should be comparatively investigated for these approaches, in order to propose a cost-effective and acceptable technique for controlling caries lesions on approximal surfaces.

The aim of this study is to evaluate the efficacy and cost-efficacy of SDF in arresting initial caries lesions compared to the resin infiltration and exclusively by flossing. Furthermore, patient discomfort, as well as parent and patient satisfaction with different treatments for initial caries lesions will be investigated.

## Methods/design

### Ethical considerations and registrations

The protocol was previously approved by the Research Ethics Committee of Dental School, University of São Paulo (protocol 140/11). Each child and adolescent must assent to participation in the study. Informed consents are obtained from their parents or guardians previous to their allocation in the study. This study protocol was also registered on ClinicalTrials.gov (NCT01477385 – November 16^th^, 2011) and written following CONSORT guidelines for randomized trials of non-pharmacologic treatment [16] and the Standard Protocol Items – Recommendations for Interventional Trials guidelines for clinical trial protocols.

### Study design

This is a randomized clinical trial, double-blinded, placebo-controlled study conducted in three-arm parallel groups. The participants will be allocated to one of the three arms in order to compare different options for arresting initial caries lesions (Figure 1). The participants and their parents/guardians, as well as the examiners, will not be aware of the patient’s allocation.

**Figure 1 Fig1:**
[figure not shown]
**CONSORT flow diagram of patient randomization.**

### Sample size calculation

To calculate the minimum sample size, we considered two possible comparisons: flossing vs. SDF/infiltration and SDF vs. infiltration. This approach follows since differences between SDF and infiltrant are expected to be lower and thus a bigger sample may be required to present statistical power. As no study has tested the SDF on approximal initial caries, we used differences between other tested treatments and/or similar treatments on other surfaces to estimate minimum expected difference among the groups tested in our protocol.

Considering flossing vs. other interventions, we considered a minimum difference of 30% [13], an alpha error of 5%, and a study power of 80%. A minimum sample size of 36 surfaces per group were found. To compare SDF and infiltrant, we considered 20% as minimum expected difference [9]. Then, the minimum sample size found was 86 surfaces. Rates considered for estimating differences among treatments were obtained from previous studies in permanent teeth. As caries progression tends to be faster in primary teeth [17], we believe similar or even smaller samples could achieve statistical power to prove existent differences in these teeth.

Considering we will include similar sample sizes for all groups, we assumed the biggest sample as reference (n = 258 surfaces). To ensure the power of the study, we added 30% to this sample to compensate possible follow-up drop-outs, totalizing a minimum sample size of 336 surfaces (112 surfaces/per group). Since child and adolescent patient characteristics were significantly different, we opted to conduct two parallel studies, with similar designs, each one including one of these groups of patients.

To compensate the clustering effect, since more than one surface may be included in each child/adolescent, we added an additional 50% on the calculation. Thus, we reached a final simple size of 504 surfaces (on average, 168 surfaces per group) to be included in this study.

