### Participant selection

A total of 141 children (3 to 10 years old) and 141 adolescents (12 to 18 years old), who seek for dental treatment in our Dental School, will be evaluated according to inclusion/exclusion criteria as follows.

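### The 30% drop-out addition covers only a 23% loss, and 504 surfaces per cohort are not reconciled with 141 participants, so 80% power for SDF versus infiltration is unsupported

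*Protocol article*

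**What the plan says.** All from the protocol article.

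- **Basis (Sample size calculation).** The calculation uses "an alpha error of 5%, and a study power of 80" per cent. For flossing against the other interventions, "we considered a minimum difference of 30" per cent, and "A minimum sample size of 36 surfaces per group were found". For the other contrast, "To compare SDF and infiltrant, we considered 20% as minimum expected difference", which gives 86 surfaces per group. The larger figure is carried forward to all three arms, 258 in total.
- **Drop-out.** With the declared purpose of protecting power, "we added 30% to this sample to compensate possible follow-up drop-outs, totalizing a minimum sample size of 336 surfaces", or 112 per group.
- **Clustering.** Because a participant may contribute several surfaces, "we added an additional 50% on the calculation". The result is 504 surfaces, on average 168 per group.
- **Scope (Abstract, Methods/design).** "A minimum sample size of 504 surfaces will be required for each subgroup". The Sample size calculation section describes two parallel studies, one in children and one in adolescents, so I read subgroup as age cohort.
- **Participants (Participant selection).** "A total of 141 children (3 to 10 years old) and 141 adolescents (12 to 18 years old") are to be evaluated against the eligibility criteria. One eligible lesion is enough for entry, and every eligible surface of an entrant is included (Inclusion criteria). Surfaces with advanced dentine lesions, and participants who refuse or show negative behaviour, are excluded (Exclusion criteria). Individuals, not surfaces, are randomised (Random allocation).

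**The concern.** Two steps in the chain do not deliver what a reader would take from them.

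First, an allowance described as 30% for drop-out reads as protection against a 30% loss. Adding 30% to the required number does not give that. The required number would have to be divided by 0.70.

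Second, the target is counted in surfaces and recruitment in people, and nothing connects the two. The mean number of surfaces per person determines whether 504 can be reached. Together with the ICC, it also determines whether a 50% allowance for clustering is enough.

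At stake is the power for SDF versus infiltration, the contrast that sets the sample size.

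**Working it through.** **1. The plan's chain reproduces.** 3 × 86 = 258; 258 × 1.3 = 335.4, rounded up to 336; 336 × 1.5 = 504; 504/3 = 168.

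The event rates behind 86 and 36 are not given. Both numbers are attainable with a two-sided 5% test, 80% power and no continuity correction: 23% versus 43% gives 86, and 15% versus 45% gives 36. I therefore take 86 effective surfaces per group as delivering 80%.

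**2. Loss covered by the 30% addition.**
- Tolerated loss: 1 − 258/336 = 23.2%.
- Remaining at 30% loss: 336 × 0.70 = 235.2, or 78.4 per group. The same follows from the final figure: 168 × 0.70/1.5 = 78.4.
- Power at effective size n per group: Φ(2.80 × √(n/86) − 1.96), where 2.80 = 1.96 + 0.84. At n = 78.4 this is 76%.
- Covering a 30% loss would take 258/0.70 = 368.6, so 369 surfaces, and 369 × 1.5 = 553.5, so 554.

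**3. Surfaces per participant.** 504/141 = 3.57, if all 141 evaluated are eligible and enter. If 120 enter, the mean needed is 504/120 = 4.2; if 100 enter, it is 5.04.

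**4. ICC that the clustering allowance can absorb.** The design effect is 1 + (m − 1) × ICC, where m is surfaces per participant. Setting it to 1.5 at m = 3.57 gives ICC = 0.5/2.574 = 0.194.

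That limit assumes equal cluster sizes. With a coefficient of variation CV it becomes 0.5/((1 + CV²) × m − 1): 0.17 at CV 0.3 and 0.14 at CV 0.5. With fewer entrants it also falls: 0.5/3.2 = 0.16 for 120, and 0.5/4.04 = 0.12 for 100.

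**5. Power for SDF versus infiltration over a range of ICC.** The ICC values are my assumptions. There are 168 surfaces per group, m = 3.57, equal clusters, and losses are of whole participants. Effective n = 168 × (1 − loss)/design effect.

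| ICC | Design effect | Power at 20% loss | Power at 23.2% loss | Power at 30% loss (effective n) |
|---|---|---|---|---|
| 0.10 | 1.257 | 88% | 86% | 83% (93.5) |
| 0.194 | 1.50 | 82% | 80% | 76% (78.4) |
| 0.30 | 1.772 | 75% | 73% | 69% (66.4) |
| 0.50 | 2.287 | 64% | 62% | 58% (51.4) |

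The highest ICC at which 80% is kept is 0.37 with no loss, (168/86 − 1)/2.574. It is 0.19 at 23.2% loss and 0.14 at 30% loss.

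**6. Flossing comparisons.** These need 36 per group. At 30% loss, 168 × 0.70 = 117.6 surfaces remain, so a design effect of up to 117.6/36 = 3.27 is tolerable. That corresponds to an ICC of (3.27 − 1)/2.574, about 0.88.

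**The case against.** The strongest reply is that nothing is miscalculated. The text says that 30% was added, not that a 30% loss is expected, and every product is correct. That stands. The article states no drop-out rate, so the 76% is conditional on reading 30% as the loss. What remains is that the allowance protects against 23%, which the text does not say and its wording does not suggest.

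A second reply is that an ICC and a mean cluster size are details a condensed article may leave to the full protocol. That also stands, and their absence alone is not the point. The point is that two numbers the article does state, 504 surfaces and 141 people per cohort, imply a demand that its entry rule of one lesion does not secure. The CONSORT diagram is not shown, so how it treats the 141 cannot be checked.

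A third reply is that the 76% treats lost participants as contributing nothing, whereas hazard ratios over all follow-up times are also planned (Statistical analysis). Late drop-outs would contribute to those, so the figure fits best the relative risk at two years.

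Three stronger readings are tempting and not supported:
- **That 80% power is overstated.** Without an ICC, power may lie on either side. At ICC 0.10 it is 83% even with 30% loss.
- **That 504 covers both cohorts.** The Sample size calculation section does not repeat the per-cohort scope, but the Abstract states it.
- **That 141 was derived from the flossing comparison**, since 3 × 36 × 1.3 = 140.4. The article does not say so, and I place no weight on it.

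**Conclusion.** The point holds in a limited form. As written, the 30% allowance is mislabelled: it preserves the required 86 per group only up to a 23% loss. If 30% loss is the planning value, power for SDF versus infiltration is about 76% at the plan's clustering factor of 1.5.

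Separately, 504 surfaces per cohort are not reconciled with 141 people to be evaluated. The pair needs a mean of at least 3.57 eligible surfaces each, and more with any screen failure. At 3.57, the clustering allowance is adequate only for an ICC up to about 0.19, less if cluster sizes vary.

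The 80% for this contrast is therefore unsupported. The conclusion rests on reading 504 as per age cohort, on 86 per group giving 80%, and on whole-participant losses. It does not extend to the flossing comparisons.

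**What to change.** In the Sample size calculation section:
- State that the allowance covers a loss of up to 23%. Alternatively, if 30% is the expected loss, restate power for SDF versus infiltration as about 76% at a clustering factor of 1.5. The 554 surfaces that would cover a 30% loss are given for information only.
- Give power over a range of ICC on both sides of 0.19, for example 0.10 to 0.50. The 0.19 should be shown as the value implied by 504, 141 and 1.5. It should not be presented as an assumption the sponsor made.
- Repeat there that 504 applies to each age cohort, as the Abstract says.

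In Participant selection, the sponsor should say whether the 141 per cohort are evaluated or enrolled, and give the mean number of surfaces per participant needed to reach 504. The article gives no basis for choosing between the two on the sponsor's behalf.

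These are text changes. The cost is that the stated power or tolerated loss becomes less favourable. The article reports that recruitment is still open, so the mean number of surfaces per participant can be watched against 3.57.

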### Participant selection

A total of 141 children (3 to 10 years old) and 141 adolescents (12 to 18 years old), who seek for dental treatment in our Dental School, will be evaluated according to inclusion/exclusion criteria as follows.

#### Inclusion criteria

Presence of at least one active initial caries lesion (scores 1, 2, or 3 according to International Caries Detection and Assessment System – ICDAS), detected by visual and tactile examination [18, 19] on approximal surfaces of primary molars for children or permanent premolar/molar for adolescents. For this purpose, surfaces will be evaluated after orthodontic rubber placement for at least 48 hours [20, 21], cleaned with dental flossing and clinically assessed by one trained and blinded examiner ([name]) after rubber removal. The approximal surfaces of interest for the study will be those that presented full contact with the adjacent tooth. All the surfaces eligible for this study will be included.

#### Exclusion criteria

i) Presence of advanced dentine caries lesions detected by bitewing radiographic examinations (radiographic scores 4, 5, or 6) [15]. Only the surfaces presenting this condition will be excluded. The other eligible surfaces in the same patient will be maintained in the sample. ii) Children or adolescents that refuse to participate in the study or present negative behaviors.

Children that presented other needs for dental treatment will be referred to treatment in our Dental School. Moreover, all individuals will receive orientation about dietary and hygiene habits.

### Random allocation

The three parallel groups of interventions are defined as SDF, caries resin infiltration, and control group (exclusively flossing instructions).

The individuals will be randomly allocated to each group according to a sequence obtained in appropriate statistical software (Medcalc software version 12.4.0.0, Ostend, Belgium). The generated sequence will be distributed in opaque and sealed envelopes, which will be opened by the operators ([name]) only at the moment of the interventions.

All individuals enrolled in the study will receive in each included surface the active intervention, the placebo therapy, and instruction for daily flossing this specific surface. When the active treatment is exclusively flossing, two placebo therapies will be used, as described below. All procedures will be performed sequentially in a same surface by trained operators ([name]), in the same appointment.

### SDF group

#### Placebo therapy

Individuals will receive sterile water application, as a placebo, maintaining the same steps of resin infiltration technique. Absolute isolation will be simulated just positioning the rubber dam on teeth, without local infiltration anesthesia and clamp.

#### Intervention

Soft tissues will be protected with petroleum jelly to avoid staining and mucosal irritation, as recommended by the manufacturer. Moisture will be controlled by using cotton rolls and saliva ejectors. The adjacent tooth will be protected by plastic or a metal strip. SDF (Cariestop® 30% – Biodinâmica Química e Farmacêutica LTDA, Brasil) will be applied with a small disposable brush for 3 min. Then, the surface will be washed for 30s [22].

At the end, patients and their parents will receive instructions for daily flossing. Children will be oriented to flossing at least one time per day, flossing each approximal surface curving the floss around the base of teeth, holding it tautly between fingers, sliding it for entire surface and not provoking gingival traumatic injuries. Parents will also receive orientation about helping their children to floss. Despite instruction being given for flossing of all interproximal spaces, the operator stresses the need of flossing the specific areas presenting initial caries lesions.

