#### Intervention

Local anesthesia and adaptation of the rubber dam and clamps will be performed. The adjacent tooth will be protected by plastic or metal strip. Hydrochloric acid 15% will be applied on the lesion for 120 s. Then, after washing and air-drying, the lesion will be dehydrated by applying 95% ethanol, followed by air-drying. The resin infiltrant will be applied on the lesion for 120 s and light-cured for 40s. Resin will be reapplied for 30s and light-cured again. All products used in resin infiltration are included in a specific kit commercialized by the manufacturers for this purpose (Icon® – Dental Milestones Guaranteed – DMG, Germany). At the end, patients and their parents will also receive instructions for daily flossing as described above.

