### Control group

#### Placebo therapy

Children will receive sterile water application, as a placebo, maintaining the same steps of used for application of SDF and for resin infiltration, without local infiltration anesthesia and clamp.

The active treatment in this group will be only instruction for daily flossing as described above.

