On the other hand, resin infiltration is a new procedure, with promising results, but it could be costly and be less accepted by patients. Previous studies have shown that flossing is less effective than infiltration, sealing, and other fluoride treatments [13, 14, 41, 42]. To the best of our knowledge, there is no study that has previously compared flossing, which would be the simplest technique to be used on approximal surfaces, with SDF. As children/adolescents who will be enrolled in this study live in an area of fluoridated water and regularly use fluoridated toothpaste, if we had not included the control group, we could not affirm which is the actual simplest and most cost-efficacious technique for approximal initial caries, which is why we decided to conduct this study in three-arm parallel groups rather than design a non-inferiority trial comparing just SDF with resin infiltration. However, depending on the results of this study a posterior effectiveness trial could be conducted. Besides, all children have been exposed to daily fluoride, have been motivated to floss every day, and are monitored regularly. Therefore, we believe that using flossing as a control group has not compromised the ethics of the trial.

To compare these three interventions, we considered important the use of placebo therapies to ensure that interventions are as similar as possible among individuals. If individuals are aware of which group they will be allocated to, they may judge more complex techniques, which demands a lot of clinical steps, as more effective and underestimate the correct daily flossing in these cases. Due to the vulnerable individuals [43] included in our study, the perfect placebo therapies could be questionable. Thus, for ethical issues, the placebo of resin infiltration will be performed just simulating the rubber dam on teeth, without local infiltration anesthesia and clamp. Despite being an imperfect placebo, simple measures like this can be enough to blind patient regarding adopted treatment [44]. Therefore, in such a type of imperfect placebo-controlled study, we expect that daily flossing is not influenced by the intervention received.

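### The operator, who has already opened the allocation envelope, stresses flossing after the procedures; giving the instruction before opening would remove an avoidable route to unequal emphasis between arms

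*Protocol article*

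**What the plan says.** Under Random allocation, the protocol article says of the sequence: "The generated sequence will be distributed in opaque and sealed envelopes, which will be opened by the operators", and that this happens only when the interventions take place. The same section provides that every participant receives, for each included surface, "the active intervention, the placebo therapy, and instruction for daily flossing this specific surface".

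The order of steps is given under each arm:

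- **SDF group, Intervention.** After application and washing: "At the end, patients and their parents will receive instructions for daily flossing". The text sets out frequency, technique and parental help, and adds that "the operator stresses the need of flossing the specific areas presenting initial caries lesions".
- **Resin infiltration group, Intervention.** After the last light-curing: "At the end, patients and their parents will also receive instructions for daily flossing as described above".
- **Control group.** After the two sham procedures are described: "The active treatment in this group will be only instruction for daily flossing as described above".

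Study design lists as unaware of allocation the participants, their parents or guardians, and the examiners. Operators are not on the list. The Discussion defends the imperfect shams and concludes that "we expect that daily flossing is not influenced by the intervention received".

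**The concern.** Flossing instruction has two roles in this trial. In the control arm it is the whole active treatment; in the other arms it is the common background against which SDF and infiltration are judged. The comparison is fair only if it is delivered with similar force in all three.

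The stated order has the operator stress the study surfaces after learning the arm. In the control arm, that operator knows that nothing else active has been given. Some operators might press the point harder there to compensate; others might do so less, out of low expectation. More emphasis in the control arm would tend to shrink the apparent benefit of SDF and infiltration, and less would tend to enlarge it. Such a difference would arise after randomisation, so randomisation does not protect against it and adjustment for baseline variables does not remove it.

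**Working it through.** The protocol states no figure for this point and none can be derived, so the check is a reading of the sections side by side.

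1. **Who learns the allocation, and when?** The operators, at the moment of the interventions (Random allocation: "which will be opened by the operators").
2. **When is the instruction given?** After the procedures in the SDF and infiltration arms, as each Intervention section states. The control section does not state the timing itself; it takes over the instruction by referring back to the earlier description. The control-arm order is therefore a reasonable inference, not an explicit statement. The note to Figure 2 lets the order of active and placebo therapies vary by group, but in the two arms where the timing is stated, the instruction follows the procedures and hence the opening.
3. **Who gives it?** The general instruction is described in the passive. Only the emphasis on lesion sites is assigned to the operator by name of role. That emphasis is the part most open to variation.
4. **Is that person blinded?** Operators are not listed in Study design, and they could not be blinded to the procedures they carry out.
5. **Is the content the same?** Nominally yes. The infiltration and control sections refer back to the SDF text, and Random allocation requires surface-specific instruction for everyone. Equal content does not guarantee equal emphasis.
6. **What does the Discussion's expectation rest on?** On the participant's side only: people who know their group may undervalue flossing, and the shams are meant to prevent that. The operator's knowledge is not discussed there.
7. **Do other parts of the plan close the gap?**
   - Use of floss is among the variables tested in Statistical analysis. Follow-up examinations has independent variables collected at baseline, with only the biofilm variables stated to be repeated at 1 and 3 months. Baseline floss use cannot reflect coaching given later.
   - The repeated biofilm measures can show a difference but cannot prevent one. Adjusting for them would condition on something measured after treatment.
   - The Discussion accepts that reported flossing may be unreliable.
   - The blinded examiner protects outcome assessment, not delivery of the instruction.

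Steps 1 to 4 establish that the emphasis comes from a person who knows the arm: explicitly for the two active arms, by cross-reference for the control arm. Steps 5 to 7 show that the existing safeguards limit the risk without closing it. Nothing in the text requires the instruction to follow the opening of the envelope.

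**The case against.** The strongest reply is that the protocol already does most of what is needed. Frequency, technique, parental help and emphasis on the lesion sites are set out once and applied to every arm, and the operators are trained. A verbatim script or a delivery record would normally sit in a full protocol or manual, so its absence from an article is not a finding. All of this stands. What remains is the order of opening and instruction, which the article itself states.

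The document also gives reason to doubt that any effect is large. The Background says that control of approximal caries by flossing alone has not been shown to be effective. Any assumed effect of coaching on progression would be a guess.

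A reader might infer more than the text supports:

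- **That the order contradicts or defeats the purpose of the shams.** It does not. The shams address what participants believe about their treatment, and they can still do that. The operator's knowledge is a separate residual risk.
- **That coaching does differ by arm.** Nothing in the document shows this; it is only left possible.
- **That SDF versus infiltration is equally exposed.** The main mechanism, an operator who knows that no active product was given, applies to the control arm. Both other arms receive one. A child's reaction to anesthesia and clamp is part of the infiltration experience, not unequal coaching.

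Finally, the same operator stays with the family after the envelope is opened and can return to the subject of flossing, so reordering is only a partial protection. That also stands.

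**Conclusion.** The point holds as an optional design improvement. The emphasis on flossing, which forms part of the control arm's only active treatment, is given by an unblinded operator after allocation is known, and this could be avoided. The exposure lies mainly in the comparison of the control arm with the two active arms.

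Its size and direction are unknown. The document gives neither the effect of flossing on progression nor the variation in how it is taught, and the planning differences in the sample size section concern the treatments, so no numerical bias is claimed.

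The conclusion rests on two readings: that the control arm follows the order described for the SDF arm, and that the operator who stresses the lesion sites is the one who opened the envelope. Both are the natural reading of the text, but neither is stated in so many words. There is no wrong figure and no internal contradiction here.

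**What to change.** - Give the complete flossing instruction, including the emphasis on the study surfaces, to every child and parent in the same appointment **before** the envelope is opened.
- In the SDF and infiltration Intervention sections, replace the wording that puts the instruction last, and state the same order explicitly for the control group.
- Tabulate the 1- and 3-month biofilm scores by arm as a descriptive check that plaque control stayed similar. Do not adjust the treatment comparison for them. Read any difference with care: the Discussion attributes an antibacterial action to SDF, so a difference need not come from flossing.
- Trial status says that recruitment is still open, so record the date of the change. Participants already treated will not benefit from it.

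**Cost.** One step moves within an existing appointment and a few words change. No extra staff, visit, procedure or data collection is needed, and the content of the instruction stays as it is. There are two downsides: the instruction is no longer the last thing the family hears, and informal coaching by the operator later in the session is not fully prevented.
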